# Study objectives

## Primary objective

| **Primary Objective:** | **Outcome Measure:** |
| --- | --- |
| To assess the efficacy of olaparib maintenance monotherapy by investigator assessed progression free survival (PFS) according to RECIST 1.1 criteria. | Time from first dosing date of olaparib to date of disease progression or death from any cause (if this occurs before disease progression) |

## Secondary objectives

| **Secondary Objective:** | **Outcome Measure:** |
| --- | --- |
| To assess the efficacy of olaparib maintenance monotherapy of *BRCA*m population by investigator assessed progression free survival (PFS) according to RECIST 1.1 criteria. | Time from first dosing date of olaparib to date of disease progression or death from any cause (if this occurs before disease progression) in BRCAm population |
| To assess the clinical efficacy of olaparib maintenance monotherapy by assessment of:  a) overall survival (OS),  b) time to investigator- assessed second progression (PFS2), or death, in patients with ovarian cancer. | a) Time from first dosing date of olaparib to date of death from any cause  b) Time from first dosing date of olaparib to date of second progression event or death from any cause (if this occurs before second progression event) |
| To assess the clinical efficacy of olaparib maintenance monotherapy by assessment of  a) time to first subsequent therapy or death (TFST),  b) time to second subsequent therapy or death (TSST) and  c) time to olaparib discontinuation or death (TDT) in patients with ovarian cancer. | a) Time from first dosing date of olaparib to date of first subsequent treatment commencement or death from any cause (if this occurs before commencement of first subsequent treatment)  b) Time from first dosing date of olaparib to date of second subsequent treatment commencement or death from any cause (if this occurs before commencement of second subsequent treatment)  c) Time from first dosing date of olaparib to date of olaparib discontinuation or death from any cause (if this occurs before discontinuation of olaparib maintenance therapy) |

## Safety objectives

| Safety Objective: | Outcome Measure: |
| --- | --- |
| To evaluate the safety and tolerability of olaparib. | AEs/SAEs  Collection of clinical chemistry/haematology parameters |

## Exploratory objectives

| **Exploratory Objective:** | **Outcome Measure :** |
| --- | --- |
| To explore biomarkers in tumor tissues or blood predictive of sensitivity/resistance to the treatment of olaparib | a) Immune-markers PD-L1 expression in tumor tissues  b) *BRCA* and HRR mutation status in the cell-free DNA from blood samples  c) HRD status in tumor samples  d）Relation between having a HRD test and patient demographic and clinical characteristics |

# PATIENT SELECTION, enrolment, restrictions, discontinuation and WITHDRAWAL

Each patient should meet all of the inclusion and none of the exclusion criteria for this study. Under no circumstances can there be exceptions to this rule.

## Inclusion criteria

For inclusion in the study patients should fulfil the following criteria:

1. Provision of informed consent prior to any study specific procedures
2. Age 18 years or over
3. Patients with platinum sensitive relapsed high grade (serous or endometrioid) epithelial ovarian cancers (including primary peritoneal and/or fallopian tube cancer)

- Platinum sensitive disease is defined as disease progression ≥6 months after completion of their last dose of platinum based chemotherapy

1. Patients should have received at least 2 previous lines of platinum containing therapy prior to enrolment:

- For the last chemotherapy course immediately prior to enrolment on the study, patients must be, in the opinion of the investigator, in response (partial or complete radiological response according to RECIST 1.1 criteria) and no evidence of a rising CA-125, following completion of this chemotherapy course.
- Pre-treatment CA-125 measurements must meet criterion specified below:
- If the first value is within upper limit of normal (ULN) the patient is eligible to be randomised and a second sample is not required
- If the first value is greater than ULN a second assessment must be performed at least 7 days after the 1st. If the second assessment is ≥ 15% more than the first the patient is not eligible

1. Have availability of 10 ml blood for germline *BRCA*m/HRRm testing and tumor sample for somatic *BRCA*m/HRRm testing: paraffin-embedded archived tumor tissue block (preferred) or, if a block is not possible, it would be better to have qualified 15 5-μm unstained sections.
2. Patients must have normal organ and bone marrow function measured within 28 days prior to administration of study treatment as defined below:

- Haemoglobin ≥ 10.0 g/dL with no blood transfusions in the past 28 days
- Absolute neutrophil count (ANC) ≥ 1.5 x 10^9^/L
- Platelet count ≥ 100 x 10^9^/L
- Total bilirubin ≤ 1.5 x institutional upper limit of normal (ULN)
- Aspartate aminotransferase (AST) (Serum Glutamic Oxaloacetic Transaminase (SGOT)) / Alanine aminotransferase (ALT) (Serum Glutamic Pyruvate Transaminase (SGPT)) ≤ 2.5 x institutional upper limit of normal unless liver metastases are present in which case they must be ≤ 5x ULN
- Patients must have creatinine clearance estimated using the Cockcroft-Gault equation of ≥51 mL/min:

Estimated creatinine clearance = (140-age [years]) x weight (kg) (x F)^a^

serum creatinine (mg/dL) x 72

^a^ where F=0.85 for females and F=1 for males.

1. Eastern Cooperative Oncology Group (ECOG) performance status 0-1.
2. Patients must have a life expectancy ≥ 16 weeks.
3. Postmenopausal or evidence of non-childbearing status for women of childbearing potential: negative urine or serum pregnancy test within 28 days of study treatment and confirmed prior to treatment on day 1.

Postmenopausal is defined as:

- Amenorrheic for 1 year or more following cessation of exogenous hormonal treatments
- Luteinizing hormone (LH) and Follicle stimulating hormone (FSH) levels in the post menopausal range for women under 50
- radiation-induced oophorectomy with last menses >1 year ago
- chemotherapy-induced menopause with >1 year interval since last menses
- surgical sterilisation (bilateral oophorectomy or hysterectomy)

1. Patients is willing and able to comply with the protocol for the duration of the study including undergoing treatment and scheduled visits and examinations.

## Exclusion criteria

Patients should not enter the study if any of the following exclusion criteria are fulfilled:

1. Involvement in the planning and/or conduct of the study (applies to both AstraZeneca staff and/or staff at the study site)
2. Previous enrolment in the present study
3. Participation in another clinical study with an investigational product during the most recent chemotherapy course
4. Any previous treatment with PARP inhibitor, including olaparib
5. Other malignancy within the last 5 years except: adequately treated non-melanoma skin cancer, curatively treated in situ cancer of the cervix, ductal carcinoma in situ (DCIS), Stage 1, grade 1 endometrial carcinoma, or other solid tumours including lymphomas (without bone marrow involvement) curatively treated with no evidence of disease for ≥5 years. Patients with a history of localised triple negative breast cancer may be eligible, provided they completed their adjuvant chemotherapy more than three years prior to registration, and that the patient remains free of recurrent or metastatic disease
6. Resting ECG with QTc > 470 msec on 2 or more time points within a 24 hour period or family history of long QT syndrome
7. Patients receiving any systemic chemotherapy or radiotherapy (except for palliative reasons) within 3 weeks prior to study treatment
8. Concomitant use of known strong CYP3A inhibitors (eg. itraconazole, telithromycin, clarithromycin, protease inhibitors boosted with ritonavir or cobicistat, indinavir, saquinavir, nelfinavir, boceprevir, telaprevir) or moderate CYP3A inhibitors (eg. ciprofloxacin, erythromycin, diltiazem, fluconazole, verapamil). The required washout period prior to starting olaparib is 2 weeks.
9. Concomitant use of known strong (eg. phenobarbital, enzalutamide, phenytoin, rifampicin, rifabutin, rifapentine, carbamazepine, nevirapine and St John’s Wort ) or moderate CYP3A inducers (eg. bosentan, efavirenz, modafinil). The required washout period prior to starting olaparib is 5 weeks for enzalutamide or phenobarbital and 3 weeks for other agents.
10. Persistent toxicities (>Common Terminology Criteria for Adverse Event (CTCAE) grade 2) caused by previous cancer therapy, excluding alopecia.
11. Patients with myelodysplastic syndrome/acute myeloid leukaemia or with features suggestive of MDS/AML.
12. Patients with symptomatic uncontrolled brain metastases. A scan to confirm the absence of brain metastases is not required. The patient can receive a stable dose of corticosteroids before and during the study as long as these were started at least 4 weeks prior to treatment. Patients with spinal cord compression unless considered to have received definitive treatment for this and evidence of clinically stable disease for 28 days.
13. Major surgery within 2 weeks of starting study treatment, or patients have not recovered from any effects of any major surgery.
14. Patients considered a poor medical risk due to a serious, uncontrolled medical disorder, non-malignant systemic disease or active, uncontrolled infection. Examples include, but are not limited to, uncontrolled ventricular arrhythmia, recent (within 3 months) myocardial infarction, uncontrolled major seizure disorder, unstable spinal cord compression, superior vena cava syndrome, extensive interstitial bilateral lung disease on High Resolution Computed Tomography (HRCT) scan or any psychiatric disorder that prohibits obtaining informed consent.
15. Patients unable to swallow orally administered medication and patients with gastrointestinal disorders likely to interfere with absorption of the study medication.
16. Breast feeding women.
17. Immunocompromised patients, e.g., patients who are known to be serologically positive for human immunodeficiency virus (HIV).
18. Patients with a known hypersensitivity to olaparib or any of the excipients of the product.
19. Patients with known active hepatitis (i.e. Hepatitis B or C) due to risk of transmitting the infection through blood or other body fluids
20. Previous allogenic bone marrow transplant or double umbilical cord blood transplantation (dUCBT)
21. Whole blood transfusions in the last 120 days prior to entry to the study (packed red blood cells and platelet transfusions are acceptable, for timing refer to inclusion criteria no.6)

Procedures for withdrawal of incorrectly enrolled patients see Section 3.4.

## Patient enrolment

Investigator(s) should keep a record of the patient screening log, of patients who entered pre-study screening.

The Investigator(s) will:

- Obtain signed informed consent from the potential patient before any study specific procedures are performed.
- Assign potential patient a unique enrolment number, beginning with ‘E#’.
- Determine patient eligibility. See Section 3.

If a patient withdraws from participation in the study, then her enrolment number cannot be reused.

## Procedures for handling incorrectly enrolled patients

Where a patient does not meet all the eligibility criteria but is incorrectly enrolled and started on treatment, the Investigator should inform the AstraZeneca study physician immediately, and a discussion should occur between the AstraZeneca study team medical advisor and the investigator regarding whether to continue or discontinue the patient from treatment.  The AstraZeneca study physician must ensure all decisions are appropriately documented.

## Methods for assigning treatment groups

Not applicable.

## Methods for ensuring blinding

Not applicable.

## Methods for unblinding

Not applicable.

## Restrictions

Patients of child bearing potential and their partners, who are sexually active, must agree to the use of two highly effective forms of contraception during the period of taking olaparib and for 1 month after last dose of study drug.

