### Contraception

Women of childbearing potential and their partners, who are sexually active, must agree to the use of one highly effective forms of contraception and their partners must use a male condom (as described in Appendix C). This should be started from the signing of the informed consent and continue throughout the period of taking study treatment and for at least 6 months after last dose of study drug(s), or they must totally/truly abstain from any form of sexual intercourse (as described in Appendix C).

For details of acceptable methods of contraception refer to Appendix C Acceptable Birth Control Methods.

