If a patient requires use of a strong or moderate CYP3A inducer then they must be monitored carefully for any change in efficacy of olaparib.

*P-gp inhibitors*

It is possible that co-administration of P-gp inhibitors (eg amiodarone, azithromycin) may increase exposure to olaparib. Caution should therefore be observed.

*Effect of olaparib on other drugs*

Based on limited *in vitro* data, olaparib may increase the exposure to substrates of CYP3A4, P-gp, OATP1B1, OCT1, OCT2, OAT3, MATE1 and MATE2K.

Based on limited *in vitro* data, olaparib may reduce the exposure to substrates of CYP3A4, 2B6, 2C9, 2C19 and P-gp.

The efficacy of hormonal contraceptives may be reduced if co administered with olaparib.

Caution should therefore be observed if substrates of these isoenzymes or transporter proteins are co-administered.

Examples of substrates include:

- CYP3A4 – hormonal contraceptive, simvastatin, cisapride, cyclosporine, ergot alkaloids, fentanyl, pimozide, sirolimus, tacrolimus and quetiapine
- CYP2B6 – bupropion, efavirenz
- CYP2C9 – warfarin
- CYP2C19 - lansoprazole, omeprazole, S-mephenytoin
- P-gp - simvastatin, pravastatin, digoxin, dabigatran, colchicine
- OATP1B1 - bosentan, glibenclamide, repaglinide, statins and valsartan
- OCT1, MATE1, MATE2K – metformin
- OCT2 - serum creatinine
- OAT3 -furosemide, methotrexate

Anticoagulant Therapy

Patients who are taking warfarin may participate in this trial; however, it is recommended that international normalised ratio (INR) be monitored carefully at least once per week for the first month, then monthly if the INR is stable. Subcutaneous heparin and low molecular weight heparin are permitted.

Anti-emetics/Anti-diarrhoeals

From screening part 2 onwards, should a patient develop nausea, vomiting and / or diarrhoea, then these symptoms should be reported as AEs (see section 6.3) and appropriate treatment of the event given.

Palliative radiotherapy

Palliative radiotherapy may be used for the treatment of pain at the site of bony metastases that were present at baseline, provided the investigator does not feel that these are indicative of clinical disease progression during the study period. Study treatment should be discontinued for a minimum of 3 days before a patient undergoes therapeutic palliative radiation treatment. Study treatment should be restarted within 4 weeks as long as any bone marrow toxicity has recovered.

Administration of other anti-cancer agents

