Appendix C Acceptable Birth Control Methods

Olaparib is regarded as a compound with medium/high foetal risk.

Women of childbearing potential and their partners, who are sexually active, must agree to the use one of highly effective forms of contraception and their partners must use a male condom (as listed below). This should be started from the signing of the informed consent and continue throughout the period of taking study treatment and for at least 6month after last dose of study drug(s), or they must totally/truly abstain from any form of sexual intercourse (see below).

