**Acceptable Non-hormonal birth control methods include:**

- Total/True abstinence: When the subject refrains from any form of sexual intercourse and this is in line with their usual and/or preferred lifestyle; this must continue for the total duration of the trial and for at least 1 month after the last dose of study drug. [Periodic abstinence (e.g., calendar, ovulation, symptothermal, post-ovulation methods, or declaration of abstinence solely for the duration of a trial) and withdrawal are not acceptable methods of contraception]
- Vasectomised sexual partner PLUS male condom. With participant assurance that partner received post-vasectomy confirmation of azoospermia.
- Tubal occlusion PLUS male condom
- IUD PLUS male condom. Provided coils are copper-banded

Acceptable hormonal methods:

- Normal and low dose combined oral pills PLUS male condom
- Cerazette (desogestrel) PLUS male condom. Cerazette is currently the only highly efficacious progesterone based pill.
- Hormonal shot or injection (eg., Depo-Provera) PLUS male condom
- Etonogestrel implants (e.g., Implanon, Norplant) PLUS male condom
- Norelgestromin / EE transdermal system PLUS male condom
- Intrauterine system [IUS] device (eg., levonorgestrel releasing IUS -Mirena®) PLUS male condom
- Intravaginal device (e.g., EE and etonogestrel) PLUS male condom

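### Section 3.8 ends contraception 1 month after the last olaparib dose and names a different method, while Section 3.8.2 and the opening of Appendix C require at least 6 months for the same women

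*Protocol*

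**What the plan says.** Three places in the protocol give a contraception rule for sexually active women of childbearing potential and their partners.

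- **Section 3.8, Restrictions.** They must agree to "two highly effective forms of contraception during the period of taking olaparib and for 1 month after last dose of study drug". The sentence does not mention a condom or refer to Section 3.8.2 or Appendix C.
- **Section 3.8.2, Contraception.** They "must agree to the use of one highly effective forms of contraception and their partners must use a male condom". This starts at the signing of consent and runs "throughout the period of taking study treatment and for at least 6 months after last dose of study drug(s"), with true abstinence as the alternative. It refers to Appendix C.
- **Appendix C, opening paragraph.** It repeats the 3.8.2 rule, including the period of at least 6 months, after stating: "Olaparib is regarded as a compound with medium/high foetal risk".

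The list of methods in Appendix C adds a further figure. For abstinence it says "this must continue for the total duration of the trial and for at least 1 month after the last dose of study drug". Every other listed method is paired with a condom, for example "Normal and low dose combined oral pills PLUS male condom".

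Section 7.7 (Concomitant and other treatments) warns: "The efficacy of hormonal contraceptives may be reduced if co administered with olaparib".

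**The concern.** A mandatory safety instruction appears in two incompatible forms, and the shorter one comes first. Section 3.8 reads as a complete rule: it names who is covered, the method and the end date. A site, or whoever drafts the consent form, could use it without suspecting that a longer rule follows.

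What is at stake is foetal exposure. Apart from the risk rating in Appendix C, Section 1.1.5 reports harm to embryofoetal survival and development at doses without significant maternal toxicity. Women of childbearing potential are eligible under Section 3.1 if their pregnancy tests are negative. The rule is still live under version 4.0, because Section 7.2 sets no maximum treatment duration, so some last doses may still lie ahead.

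**Working it through.** No statistical figure is involved. The check is a side-by-side reading of current text and one subtraction.

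| | Section 3.8 | Section 3.8.2 and opening of Appendix C |
|---|---|---|
| Population | Sexually active, childbearing potential, and partners | The same |
| Start | Period of taking olaparib | Signing of consent |
| Method | Two highly effective forms | One highly effective form plus male condom, or true abstinence |
| End after last dose | 1 month | At least 6 months |

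**Duration.** 6 − 1 = 5 months. At 30.44 days per month, 5 × 30.44 / 7 = 21.7, or about 22 weeks.

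**Method.** Appendix C lists 3 non-hormonal methods other than abstinence (vasectomised partner, tubal occlusion, copper-banded IUD) and 7 hormonal ones (combined pills, desogestrel pill, injection, implant, transdermal system, intrauterine system, intravaginal device). That makes 3 + 7 = 10, and all 10 carry a male condom.

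The protocol nowhere calls the condom highly effective. One method plus a condom therefore does not satisfy two highly effective forms, and two highly effective forms without a condom do not satisfy 3.8.2. Neither rule contains the other. Read alone, Section 3.8 would allow two hormonal methods with no barrier, which sits badly with the interaction warning in Section 7.7.

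**Abstinence bullet.** This is a smaller point. The bullet sets two joint conditions: the whole trial, and at least 1 month after the last dose. If a woman's participation ends t months after her last dose, the bullet requires max(t, 1) months, so the shortfall against 6 months is max(0, 6 − max(t, 1)):

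- t ≤ 1: 6 − 1 = 5 months
- t = 3: 6 − 3 = 3 months
- t ≥ 6: 0

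Under Section 3.9.1, stopping olaparib does not take a patient out of the study, so most women would have no shortfall. The gap appears where consent is withdrawn around the time of stopping, or where olaparib continues after study closure (Sections 4.4.5 and 7.8), if the appendix is still applied then.

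**The case against.** The strongest reply is that the longer rule is hard to miss. Section 3.8 is a one-sentence introduction. The dedicated subsection follows after a single line on grapefruit juice, gives more detail and points to Appendix C, which repeats it. Keeping to 6 months also satisfies the 1-month minimum. An unsafe pair of methods would pass only if 3.8.2 and Appendix C were both ignored. This lowers the chance of harm but does not remove the contradiction: no text ranks the two rules, and the longer period does not reconcile the methods. A woman could meet both rules only by using two highly effective methods and a condom together until 1 month after the last dose, then one method and a condom to 6 months. Nothing suggests that this was meant.

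A second reply is that 6 months is not proved to be the intended figure. That is fair. One month appears in Section 3.8, in the abstinence bullet and in the conception follow-up window of Section 6.6.1; 6 months appears in 3.8.2 and the opening of Appendix C. The repetition also shows that the shorter figure is not one stray slip, so sites cannot simply discount it.

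A third reply is that few women may be exposed. Patients have had at least two platinum lines, and Section 3.1 counts surgical sterilisation and chemotherapy-induced menopause of more than a year as postmenopausal. The consent form is not available, so what women were actually told is unknown. These points limit the weight of the finding but not its correctness.

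The window in Section 6.6.1 is not a defect in its own right: Section 6.6 already makes all pregnancies reportable, and 6.6.1 requires the outcome of every pregnancy to be followed.

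**Conclusion.** The concern holds and should be fixed. Section 3.8 contradicts its own subsection and the opening of Appendix C on start, method and duration. The gap in duration is 5 months for a woman counselled from Section 3.8 alone; one who is also counselled from 3.8.2 gets the longer period. The abstinence bullet is a secondary inconsistency, with a shortfall of 0 to 5 months depending on when participation ends.

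Taking 6 months as the correct period is an assumption. It is the cautious choice and has the dedicated subsection behind it. The number of women affected cannot be derived from the protocol. The effect is on participant safety instructions only; the primary endpoint, sample size and analyses do not change.

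**What to change.** - **Section 3.8:** replace the sentence with the 3.8.2 rule, namely one highly effective method plus a male condom from signing of consent until at least 6 months after the last dose, or true abstinence for the same period, with a reference to Appendix C.
- **Appendix C, abstinence bullet:** change 1 month to 6 months, so that women who leave the trial early or take olaparib after closure are also covered.
- **Consent form:** check it for the 1-month wording and correct it if present.
- **Optional, for consistency only:** extend the conception window in Section 6.6.1 to 6 months.

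The sponsor should confirm that 6 months is the intended period when making the change. The cost is text alignment in the next amendment, and in the consent form if it repeats the shorter period. The main changes alter neither data collection nor analysis.
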